## Abstract

**Background:**

Hyperuricemic nephropathy is a highly prevalent kidney disease induced by excessive accumulation and deposition of monosodium urate in kidney, which contributes to the loss of kidney function. The Jiangniaosuan formulation (JNSF) is a Chinese herbal medicine treatment. The aim of this study is to evaluate its efficacy and safety among patients with hyperuricemic nephropathy at chronic kidney disease (CKD) stages 3–4 and with obstruction of phlegm turbidity and blood stasis syndrome.

**Methods:**

Our research is designed as a single-centre, double-blinded, randomized, placebo-controlled trial for 118 patients diagnosed with hyperuricemic nephropathy at CKD stages 3–4 and with obstruction of phlegm turbidity and blood stasis syndrome in mainland China. Patients are to be randomized into two groups: either the intervention group which receives JNSF 20.4 g/day combined with febuxostat 20–40 mg/day, or the control group which receives JNSF placebo 20.4 g/day combined with febuxostat 20–40 mg/day. The intervention will be carried on for 24 weeks. The change in estimated glomerular filtration rate (eGFR) is set as the primary outcome. Secondary outcomes include changes in serum uric acid, serum nitric oxide, urinary albumin/creatinine ratio, urinary *N*-acetyl-β-D glucosaminidase, urinary β2 microglobulin, urinary retinol binding protein and TCM syndromes in 24 weeks. Statistical analysis will be formulated by SPSS 24.0.

**Discussion:**

The trial will conduce to the comprehensive assessment in the efficacy and safety of JNSF among patients diagnosed with hyperuricemic nephropathy at CKD stages 3–4, and provide a clinical method available on systems of the combination of modern medicine and TCM.

## Background

1

Hyperuricemic nephropathy (HN) is a pathological condition induced by hyperuricemia (HUA) or gout. Hyperuricemia is caused either because of the excessive production or decreased excretion of uric acid (serum uric acid >0.41 mmol/L or 6.8 mg/dL) [1]. Classically, the accumulation of monosodium urate crystals in kidney tissues cause inflammatory reactions that contribute to kidney damage. The incidence of gout is in the range of 0.6–2.9/1000 individuals per year worldwide, and the adult prevalence ranges from 0.68% to 3.90% [2]. The prevalence rate of gout in Chinese adults is 1.1%; a trend of increase has been observed from 1.0% in 2000–2005 to 1.3% in 2010–2016 [3]. From 2000 to 2014, the aggregate prevalence has been approximately 13.3% and 1.1% in patients with hyperuricemia and gout in mainland China [4]. The increase in the incidence of hyperuricemia and gout has been accompanied by an increase in the number of patients with hyperuricemic nephropathy. This poses a serious threat to health of individuals. Approximately 100% of patients with gout exhibit renal damage during autopsy [5]. In general, hyperuricemic nephropathy is a frequent occurrence observed in different types of progressive chronic kidney disease (CKD). The expensive charge for hemodialysis and kidney transplantation results in a tremendous financial burden both to individuals and society. Therefore, it is particularly important to focus on the delay of the further progression of CKD.

At present, the conventional treatment for hyperuricemic nephropathy mainly involves the administration of urate-lowering therapy (ULT) and symptomatic treatment of complications, adverse events, and toxic side effects. Xanthine oxidase inhibitors (XOI) are considered first-line ULT [6], including allopurinol and febuxostat. However, either of them did not retard the decline of eGFR in comparison with placebo in CKD stages 3–4 patients [7,8].

Currently, several treatment alternatives, including traditional Chinese medicine (TCM), which is a supplementary therapy for hyperuricemic nephropathy, are available. During the treatment with TCM, phlegm turbidity stasis resistance is considered to be the main pattern observed in stages 3–4 (advanced stage) CKD patients with hyperuricemic nephropathy based on syndrome differentiation. The Jiangniaosuan formulation (JNSF) contains seven herbs, i.e., 10 g Semen Vaccariae, 10 g Semen sinapis, 15 g Semen plantaginis, 10 g Dioscoreae hypoglaucae rhizoma, 10 g Fructus crataegi, 15 g Radix clematidis, and 10 g Radix et rhizoma rhei. JNSF is mainly used to dissolve phlegm and reduce turbidity, promote blood circulation, and promote collaterals, which is in accordance with the pattern observed in patients at advanced stages of hyperuricemic nephropathy.

Our previous work has demonstrated that JNSF can lessen urate crystallization, suppress renal inflammation and improve renal function in rats with hyperuricemic nephropathy, and the changes could be contributed to suppressing the TLR4/NF-κB signaling pathway [9]. However, no evidence-based clinical study has appraised the efficacy and safety of the clinical application of JNSF for the therapy of hyperuricemic nephropathy. Consequently, we conduct a randomized, double-blinded, placebo-controlled clinical approach to assess whether clinical efficacy could be improved with the use of JNSF for the treatment of stages 3–4 CKD patients with hyperuricemic nephropathy. This would also provide an effective approach and help us accumulate evidence-based medical support for the treatment of hyperuricemic nephropathy in stages 3–4 CKD patients using traditional Chinese medicine.

## Methods and design

2

### Trial design

2.1

This study will be a prospective, single-centre, double-blinded, randomized, placebo-controlled trial involving stages 3–4 CKD patients with hyperuricemic nephropathy from mainland China. Patients are to be randomized into either the Jiangniaosuan formulation (JNSF) and febuxostat group or the JNSF placebo and febuxostat group. The intervention will be carried on for 24 weeks. This is designed as a superiority trial with allocation ratio = 1/1. The design of this study is laid out in Fig. 1.

**Fig. 1 fig1:**
[figure not shown]
Flowchart showing the process to be followed for the JNSF study during the intention-to-treat analysis.

### Ethics and registration

2.2

This study protocol (Version 2021.01.20.01) has been approved by Ethics Committee of Shuguang Hospital affiliated with Shanghai University of TCM (Approval Number: 2021-942-17-01). The trial has been registered with the Chinese Clinical Trials Register (ChiCTR2100049048) on July 20, 2021. The chief investigators are those clinicians who have acquired relevant qualifications. Before, during or after the trial, the personal data and biospecimens of enrolled participants will not be revealed to any third party. The results will be disseminated through scientific meetings and published in peer-reviewed journals.

### Participating centre

2.3

The study will recruit 118 outpatients or inpatients from the Department of Nephrology or Rheumatology at Shuguang Hospital affiliated to Shanghai University of Traditional Chinese Medicine.

### Study population

2.4

We will enroll 118 stage 3–4 CKD patients diagnosed with hyperuricemic nephropathy with phlegm-turbid obstruction and blood stasis syndrome.

### Sample size

2.5

The sample size is issued from the primary outcome that is an alteration in baseline estimated glomerular filtration rate (eGFR). According to a previous report [8], the average eGFR value of the control group is estimated to be 34.7 mL/min/1.73 m^2^. After treatment with JNSF, the value for the intervention group could be increased by 10 mL/min/1.73 m^2^, and its standard deviation would be approximately 18.1 mL/min/1.73 m^2^. If we set the type 1 risk level at 5% and the power at 80%, we calculated that the minimum sample size for each group is 53 participants, using the formula: $t=\frac{\bar{x_{1}}-\bar{x_{2}}}{\sqrt{\frac{\left(n_{1}-1\right)s_{1}^{2}+\left(n_{2}-1\right)s_{2}^{2}}{n_{1}+n_{2}-2}\left(\frac{1}{n_{1}}+\frac{1}{n_{2}}\right)}}$. Assuming a drop-out rate of approximately 10%, we determined that the sample size should be increased to 59 in both groups, to include a total of 118 patients.

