#### Diagnostic criteria for TCM syndrome differentiation

2.8.3

Based on an evaluation of the diagnosis, syndrome differentiation, and curative effect in patients with hyperuricemic nephropathy (trial Scheme) [10], a patient, to be diagnosed with the obstruction of phlegm turbidity and blood stasis syndrome, has to perform no less than three of the primary symptoms listed below.

Primary symptoms.◆Pain or swelling in the joints◆Joint stiffness and deformation, possibly with subcutaneous gout nodules◆Impaired flexion and extension of joints◆Fatigue and swelling limbs◆Sticky and greasy in the mouth◆Increased nocturia◆Frequent urination◆Waist sinking and pain◆A red or dark tongue with ecchymosis◆A yellow and greasy coating of the tongue◆A string-like and slippery pulse

Inclusion criteria and exclusion criteria are listed below (Table 1).

**Table 1 tbl1:** Eligibility criteria for the trial.

Inclusion criteria
To be eligible for participation patients must be:
◆ Individuals diagnosed with hyperuricemic nephropathy beyond three months as listed above, at the same time diagnosed with obstruction of phlegm turbidity and blood stasis syndrome in TCM
◆ Aged between 18 and 75 years
◆ The eGFR value ≥ 15 mL/min/1.73 m^2^ and <60 mL/min/1.73 m^2^
◆ Should be able to provide serum or urine pregnancy test results (for females), 24 h earlier than JNSF administration
◆ Should be able to provide the investigators with informed consent in written form for trial enrollment

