### Primary outcome

2.11

The primary outcome is the eGFR value, and it is calculated using the CKD-EPI creatinine equation, to evaluate the kidney function before and after the intervention on visit 1 to 4 (listed in Table 3).

**Table 3 tbl3:** The measurement items and study procedure.

Items	Screening	Treatment			
Timepoint	V0(-1 weeks)	V1(0 week)	V2(4 weeks)	V3(12 weeks)	V4(24 weeks)
Informed consent	X				
Inclusion/exclusion criteria	X				
Demographic data	X				
Medical history	Χ				
Drug combination	Χ	Χ	Χ	Χ	Χ
Randomization		Χ			
Allocation		Χ			
Physical examination	Χ	Χ	Χ	Χ	Χ
TCM symptoms	Χ	Χ	Χ	Χ	Χ
Kidney function (eGFR, Scr, BUN, SUA)	Χ	Χ	Χ	Χ	Χ
Serum electrolytes	Χ	Χ		Χ	Χ
24-h urine test	Χ	Χ		Χ	Χ
UACR	Χ	Χ		Χ	Χ
Renal tube function	Χ	Χ		Χ	Χ
Inflammatory mediators		Χ		Χ	Χ
Renal ultrasound	Χ	Χ			Χ
Blood, urine and stool routine	Χ	Χ		Χ	Χ
Hepatic function	Χ	Χ		Χ	Χ
Electrocardiogram	Χ	Χ		Χ	Χ
Adverse events			Χ	Χ	Χ
Drug distribution		Χ	Χ	Χ	
Drug collection			Χ	Χ	Χ

X indicates that data need to be collected during the visit.

TCM, traditional Chinese medicine; eGFR, estimated glomerular filtration rate; Scr, serum creatinine; BUN, blood urea nitrogen; SUA, serum uric acid; UACR, urine microalbumin to creatinine ratio.

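### The sample size is worked out on eGFR levels while the declared primary outcome is change in eGFR, so the stated 80% is not shown to be the power for that outcome

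*Protocol article*

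**What the plan says.** The abstract declares a change outcome: "The change in estimated glomerular filtration rate (eGFR) is set as the primary outcome". Section 2.5 (Sample size) takes the same starting point: "The sample size is issued from the primary outcome that is an alteration in baseline estimated glomerular filtration rate (eGFR").

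The inputs in section 2.5 are then worded as levels. For control, "the average eGFR value of the control group is estimated to be 34.7" mL/min/1.73 m². With JNSF, "the value for the intervention group could be increased by 10" units, "and its standard deviation would be approximately 18.1 mL/min/1.73" m². With a type 1 error of 5% and power of 80%, the section arrives at 53 per group. A drop-out allowance of about 10% raises this to 59 per group and 118 in total. The formula printed beside the calculation is the pooled two-sample t statistic.

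Section 2.11 words the outcome differently: "The primary outcome is the eGFR value, and it is calculated using the CKD-EPI creatinine equation", assessed before and after the intervention at visits 1 to 4. Section 2.15 lists t-tests or rank-sum tests and a repeated measures ANOVA, without saying which is the primary comparison or on which scale it is made.

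On the source of the 10 units, the Background states that "no evidence-based clinical study has appraised the efficacy and safety of the clinical application of JNSF".

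**The concern.** A change from baseline and a level measured once have different standard deviations. Which is larger depends on how strongly a patient's baseline and week-24 eGFR are correlated. Section 2.5 names the change as its basis but gives no expected change, no SD of change and no correlation. The 80% is therefore attached to an outcome for which it was not derived.

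The practical stake is in the reading of the result. If the trial is null, readers will take from section 2.5 that a difference of 10 units would have been found with 80% probability and that smaller differences were out of reach. For the declared outcome neither statement has been established. The printed formula does not help, because a t statistic has no term for alpha or power and cannot return a sample size.

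**Working it through.** **Inputs from the protocol.** Difference 10, SD 18.1, type 1 error 5%, power 80%, drop-out 10% (section 2.5); allocation 1:1 (section 2.1). Sidedness is not stated.

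**Step 1: reproduce the stated figure.** The normal approximation for two means, two-sided, is n = 2(1.96 + 0.8416)² × 18.1² / 10² = 51.4, so 52 per group. With the noncentral t distribution, n = 52 gives 79.7% power and n = 53 gives 80.4%, so 53 per group. A one-sided test would need only 42. Then 53/0.9 = 58.9, so 59 per group, and 2 × 59 = 118. All three stated figures reproduce as a two-sided t-test with SD 18.1.

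**Step 2: the same trial with an unadjusted change as outcome.** If the level SD is 18.1 at both times and r is the correlation between baseline and week 24, the SD of change is 18.1 × √(2(1 − r)). The protocol does not give r, so it is varied here as an assumption. Power is for a difference of 10 with 53 per arm.

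| r (assumed) | SD of change | Power with 53 per arm | n per arm for 80% |
|---|---|---|---|
| 0 | 25.6 | 51% | 104 |
| 0.3 | 21.4 | 66% | 73 |
| 0.5 | 18.1 | 80% | 53 |
| 0.7 | 14.0 | 95% | 32 |
| 0.8 | 11.4 | 99.4% | 22 |
| 0.9 | 8.1 | above 99.9% | 12 |

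The stated 80% coincides with the power for an unadjusted change only at r = 0.5, where 2(1 − r) = 1.

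**Step 3: the same trial with adjustment for baseline eGFR.** The residual SD is 18.1 × √(1 − r²). It is the same whether the outcome is week-24 eGFR or its change. With 53 per arm, the noncentral t gives 80% power at a difference of 0.549 × residual SD.

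| r (assumed) | Residual SD | Power for 10 units | Detectable difference at 80% |
|---|---|---|---|
| 0 | 18.1 | 80% | 9.9 |
| 0.5 | 15.7 | 90% | 8.6 |
| 0.7 | 12.9 | 98% | 7.1 |
| 0.8 | 10.9 | 99.7% | 6.0 |
| 0.9 | 7.9 | above 99.9% | 4.3 |

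Because √(1 − r²) never exceeds 1, 53 per arm gives at least 80% power for 10 units at every value of r.

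**The case against.** The strongest reply is that section 2.11 calls the primary outcome the eGFR value. If week-24 values were simply compared between groups, an SD of levels would be the right input and 80% would be the power of that comparison. This stands as a reading of section 2.11, but not as a defence of the protocol. The abstract and section 2.5 itself name the change, and section 2.11 also speaks of before and after the intervention.

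A second reply is that 18.1 might be an SD of change. The wording and the pairing with a mean level of 34.7 point to a level SD, but the cited report is not at hand. If 18.1 were an SD of change, 53 would be right for the change, the level mean would play no part, and the protocol would need to say so. The formula would still be the wrong one.

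Third, a t statistic printed in place of a sample-size formula can be called a reporting slip in a condensed article, since the result reproduces. That is fair as to its weight. It remains an error in the text.

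Several stronger readings are tempting and are not supported:

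- *The calculation is arithmetically wrong.* It is not; 53, 59 and 118 all reproduce.
- *The trial is underpowered.* For an unadjusted change this is so only if r is below 0.5. Above that, power for 10 units exceeds 80%.
- *18.1 is too large for patients enrolled between 15 and 60.* A uniform spread over that range has SD 45/√12 = 13.0, but that is no upper limit. With mean 34.7 the SD could reach √(19.7 × 25.3) = 22.3, and week-24 values may leave the entry range.
- *The plan is to analyse levels, so power for smaller differences is poor.* Section 2.15 does not fix that analysis.
- *There is no clinical experience behind the 10 units.* The Background says no evidence-based clinical study has been done, and the Discussion mentions the authors' own clinical observations. These carry no figure, so the 10 is an assumption without cited data; more than that cannot be said.

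**Conclusion.** The point holds as a mismatch between the declared outcome and the scale of the sample-size inputs. The stated 80% is the power for comparing eGFR levels. For an unadjusted change it could be anywhere from 51% (r = 0) to above 99% (r = 0.8 to 0.9), and the document does not say where in that range it falls. No single corrected sample size can be given.

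This rests on three assumptions: that 18.1 is a level SD, that it applies at baseline and at week 24 alike, and that r lies somewhere between 0 and 0.9. The number of patients need not change, because a baseline-adjusted comparison with 53 per arm keeps at least 80% power for 10 units whatever r is. The paragraph should be corrected, since it will govern how a null result is read.

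**What to change.** 1. Reconcile the abstract, section 2.5 and section 2.11 on one endpoint: eGFR at week 24, or its change from baseline, compared between groups with adjustment for baseline eGFR.
2. Keep 118 patients. Keep the difference of 10 and the SD of 18.1 as the basis on which the number was set. Say that 18.1 is the SD of levels, if the cited report confirms it, and that 10 is an assumption without clinical data behind it.
3. Replace the t statistic with a sample-size formula on the endpoint's scale, using residual SD = SD × √(1 − r²), and state that the test is two-sided.
4. Report the difference detectable at 80% power with 53 per arm over a range of r: about 9.9 at r = 0, 8.6 at 0.5, 7.1 at 0.7, 6.0 at 0.8 and 4.3 at 0.9. Give a source for r if one is found.

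The cost is one rewritten paragraph and a matching endpoint wording in two other places. No patients, visits or measurements are added, since section 2.10 and Table 3 already provide eGFR at baseline and week 24.

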### Randomization procedures

2.6

Potential participants will be screened for eligibility a week anterior to study randomization. Participants will be randomly assigned as a consequence of a randomization schedule to receive JNSF treatment coupled with febuxostat (intervention group) or JNSF placebo treatment coupled with febuxostat (control group).

These treatments are changed into two groups A and B by the independent statistician. A random numbering (1:1) is formulated based on complete randomization with a block size of 4 via SPSS software.

### Blinding

2.7

This trial will be conducted in a double-blinded manner. The allocation process is blind to all individuals, including the physicians, clinical trial pharmacists, investigators, and patients, apart from the independent statisticians as they generate the random numbering.

The placebo granules and the JNSF granules will be tantamount in the matter of packaging, shape, color, and taste. The pharmaceutical company will pre-paste consecutive random numbers on the package based on the randomization schedule dispatched from the independent statistician. Patients will be given the package of JNSF or the placebo in the order of their visit by clinical trial pharmacists. The double-blind trial is divided into a primary unblinding and a secondary unblinding after the end of the last patient follow-up. The first level of unblinding is to reveal whether each patient belongs to group A or B and to facilitate comparisons between the groups by the statistician. After the statistical conclusions are obtained, a secondary unblinding is required to be informed of the medication use in each group. The independent statistician will provide the principal investigator with a set of sealed and externally numbered envelopes, which inside is the medication used. In case the serious adverse events (SAEs) occur, early broken blinding is performed by the principal investigator to estimate whether there is a connection to the intervention drug, overdose, serious drug interactions with combined drugs or the urgent need to adopt a resuscitation plan.

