### Data and safety monitoring

2.14

The investigators will receive unified training and data monitoring committee (DMC) will be set up with experienced physicians and statisticians, who have no competing interests, to conduct monitoring once every three months for the entire research process. The trained investigators will fill out the case report form (CRF), and use EpiData 2.1a software to establish the special database system for this trial according to the items in the CRF. Two independent data administrators will type the data and conduct audits to ensure that the data in the database is consistent with the results in the CRF.

The participant will be monitored in the circumstance that an adverse event (AE) occurs, until their AE disappears. As patients diagnosed with Hyperuricemic Nephropathy frequently suffer from gout attacks, we will advise patients to oral intake anti-inflammatory drug or low-dose corticosteroids until the pain is relieved. AEs will be reported to the principal investigator to assess and the IRB. The investigator will conduct a follow-up interview and record the results supposing that the intervention induces the AE. Safety monitoring results will be reported to principal investigator weekly and the IRB.

The following are potential events related to the safety of the intervention.◆The eGFR is decreased by ≥ 50%◆The serum creatine levels is doubled than the previous blood test◆The patient is in the progression of CKD stage 5◆The patient occurs serious cardiovascular or cerebrovascular event◆The heart rate of patient is less than 40 bpm◆The patient occurs an unexpected event that is supposed to the intervention by the physicians

The following are potential SAEs.◆The patient occurs fatal or life-threatening complications◆The patient is dead or persistent and significant disabled◆The patient is hospitalized or receive large-scale medical intervention to prevent progression◆The patient develops any event that physicians diagnose to be significantly hazardous or harmful

The trial can be terminated for the following reasons.◆The number of enrolled patient is insufficient◆The allocation codes are unwrapped or the process of blinding has been nullified if the proportion of unsealed envelopes with emergency plans is more than 20% during the trial◆SAEs are supposed to associated with the intervention drug in the trial, which may signify that the safety of the drug has serious flaws

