### Statistical analysis

2.15

The independent statisticians will formulate a formal and detailed plan for statistical analysis prior to locking the database. Comparing the baseline demographic data of each group will use with a χ^2^ test or Student's t-test. The means ± standard deviations or medians will express continuous variables, and an independent *t*-test or the Wilcoxon rank sum test will be used to analyze differences of such variables. Repeated measures ANOVA will be built for these outcomes. The numbers and percentages will express categorical variables, and the Fisher exact test or the Mann-Whitney *U* test will be used to calculate and compare differences in such variables respectively. The missing data will be handled with multiple imputation. According to the intention-to-treat principle, all patients enrolled will be embraced in the primary analysis. An independent statistician will use SPSS 24.0 to perform the statistical analysis. Calculations will be performed using GraphPad Prism 6.01 software.

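### Judging whether an SAE is drug-related is itself a ground for the principal investigator to open the code, so SAE attribution would be made knowing the arm

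*Protocol article*

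**What the plan says.** Four parts of the protocol article bear on this.

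- **Section 2.7 (Blinding), code-breaking.** "In case the serious adverse events (SAEs) occur, early broken blinding is performed by the principal investigator to estimate whether there is a connection". The link meant is one with the study drug. The same sentence then adds overdose, serious interactions with other drugs, and an urgent need for resuscitation. These are joined by 'or', so urgent need is one ground among several and not a condition for the others.
- **Section 2.7, custody.** "The independent statistician will provide the principal investigator with a set of sealed and externally numbered envelopes, which inside is the medication used".
- **Section 2.14 (Data and safety monitoring).** Adverse events go to the principal investigator for assessment, and to the IRB. The list of potential SAEs includes this item: "The patient is hospitalized or receive large-scale medical intervention to prevent progression". Among the reasons for which the trial can be ended are SAEs thought to be associated with the study drug and, separately, loss of blinding "if the proportion of unsealed envelopes with emergency plans is more than 20% during the trial".
- **Sections 2.6, 2.7 and 2.15, statisticians.** Section 2.6: "These treatments are changed into two groups A and B by the independent statistician". Section 2.7 blinds everyone "apart from the independent statisticians as they generate the random numbering". Section 2.15: "The independent statisticians will formulate a formal and detailed plan for statistical analysis prior to locking the database", and an independent statistician then runs the analysis.

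**The concern.** Relatedness is a judgement, and blinding protects it only if the judgement comes first. Here the envelope is opened in order to make it. An assessor who knows that the patient received placebo will rarely call the event related to JNSF. An assessor who knows that the patient received JNSF may be drawn either way, towards blaming the product or towards excusing it. The count of drug-related SAEs can then differ between arms even if the drug has no effect on SAEs.

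Two things are at stake. Safety is half of the trial's stated aim, so this comparison will be reported. The same judgement also feeds a reason for ending the trial. The ground is not narrow, since hospitalisation qualifies as a potential SAE and section 2.3 admits inpatients as well as outpatients.

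**Working it through.** The point changes no planned figure. The sample size in section 2.5 reproduces: with a difference of 10, an SD of 18.1 and a two-sided 5% t-test, power is 79.7% at 52 per arm and 80.4% at 53, so 53. Then 53 / 0.9 = 58.9, so 59 per arm and 118 in all. The rest is a comparison of passages.

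**1. Who judges, and what that person knows**

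| Question | Answer in the text | Section |
|---|---|---|
| Who assesses adverse events? | Principal investigator | 2.14 |
| Who holds the envelopes? | Principal investigator | 2.7 |
| Who opens them at an SAE? | Principal investigator | 2.7 |
| First purpose listed for opening? | To judge a link with the study drug | 2.7 |
| What can follow from that judgement? | Ending the trial, if SAEs are thought drug-related | 2.14 |

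One role holds, opens and judges, in that order. No sentence requires a causality assessment to be recorded before the envelope is opened.

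**2. Why the order matters**

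Let r_J and r_P be the proportions of SAEs judged related to the study drug in the JNSF and placebo arms. Suppose JNSF has no effect on SAEs.

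- Judged blind, the same standard meets the same kind of events, so r_J = r_P in expectation.
- Judged with the arm known, r_P is pushed towards 0, while r_J follows the assessor's prior view of the product. The expected difference r_J − r_P is then in general not 0, although the drug does nothing.

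The size depends on the SAE rate and on the assessor's behaviour. The document gives neither, so I put no number on it.

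**3. Which openings count towards the 20% rule**

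More than 20% of 118 means 0.20 × 118 = 23.6, so 24 openings (23/118 = 19.5%; 24/118 = 20.3%), taking one envelope per patient. Section 2.14 speaks of envelopes opened under emergency plans. Section 2.7 also allows opening for causality, overdose and interactions, without saying whether these are emergencies. The same set of openings could therefore be counted in two ways, and the two sections must be reconciled.

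**4. The two-level unblinding**

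The first level shows A or B, and the second shows which treatment each letter is. This masks an analyst who did not set the letters. It masks nothing for the person who set them (section 2.6). The text uses the same role name for making the list, writing the analysis plan and running the analysis, and does not say whether these are different people.

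**The case against.** The strongest reply is that opening a code at an SAE is ordinary practice. Overdose, interactions and urgent need are conventional grounds, and the quoted sentence contains them. That is right, and those grounds are not criticised here. The reply does not reach the first ground, because estimating causality needs no code and is better done without it.

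A second reply is that the harm is limited. The primary outcome is a laboratory eGFR, and several of the listed safety events are objective, such as an eGFR fall of at least 50% or a heart rate below 40. This stands, and it confines the point to SAE attribution and the termination criterion that uses it.

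Four stronger readings are tempting, but the document does not support them.

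- **The blind is broken trial-wide.** The rule touches only SAE patients whose envelopes are opened.
- **The people who hold the code also analyse the data.** No passage says so. Section 2.15 has 'an' independent statistician run the analysis, who may be a second person, and an article commonly leaves the division of roles to the full protocol. Only a clarification can be asked for.
- **SAE openings will probably trip the 20% limit.** No SAE rate is given. Even if every SAE led to a counted opening, the chance of 24 or more is below 0.1% at an assumed SAE risk of 5–10% and about 50% at 20%, so the answer is whatever one assumes. The rule also refers to emergency openings, and it says the trial can be ended, not that it will be.
- **The fixed block of 4 exposes other patients.** One opening moves each of the other three in the block from 1/2 to 2/3 for the opposite arm. But packages are pre-numbered and given in visit order, and no passage says that the principal investigator scores symptoms. Calling the scheme complete randomization is loose wording. Varying block sizes would be a preference, and a new list would mean relabelled packages and new envelopes.

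**Conclusion.** The point holds in a limited form. Followed as written, sections 2.7 and 2.14 together have SAE causality judged by someone who has just learned the arm, and that judgement feeds both the safety comparison and a reason for ending the trial. This should be corrected. It does not threaten the primary analysis.

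The conclusion assumes that the principal investigator named in the two sections is the same role, as the text indicates, and that no fuller document requires a blinded assessment first. If one does, section 2.7 of the article still misstates the procedure. The bias cannot be quantified from the document, and its direction in the JNSF arm is open. The unclear count under the 20% rule and the unstated separation of statisticians are secondary wording points.

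**What to change.** 1. In section 2.7, require the causality of every SAE to be recorded blind, with date and time, before and independently of any code break. Remove causality assessment as a reason in itself for opening an envelope. Leave the other listed grounds as they are.
2. Reconcile section 2.7 with the 20% rule in section 2.14 by stating which openings count towards the limit.
3. State in section 2.7 or 2.15 that the statistician who makes the list and sets the A and B labels is not the one who writes the analysis plan and analyses the data. Otherwise the two-level unblinding masks nothing for that person.

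The cost is a protocol amendment of a few sentences, one dated field on the SAE form, and a division of tasks among independent statisticians whom the article already mentions in the plural. No extra patients, visits, packages or envelopes are needed, and the randomization list stays as it is.
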